### Adverse events reporting and analysis

The collection and reporting of AEs as measured by National Cancer Institute Common Terminology Criteria for Adverse Events (CTCAE), version 5.0 [33] will be in accordance with the Research Governance Framework for Health and Social Care and the requirements of the National Research Ethics Service. Definitions of different types of AEs are listed in Appendix 8. The reporting period for AEs will be between the date of commencement of protocol defined treatment until 28 days after the administration of the last protocolised drug. SAEs will be reported from the date of signing the Informed Consent Form to 28 days after the last dose of IMP. The investigator should assess the seriousness and causality (relatedness) of all AEs experienced by the patient with reference to the protocol. Abnormal laboratory findings should only be reported if the event results in the early discontinuation of trial treatment, a dose modification, or interruption. If a laboratory abnormality is one component of a diagnosis or syndrome, then only the diagnosis or syndrome should be recorded as an AE.

Pre-existing conditions should only be reported if the condition worsens by at least one CTCAE grade.

The following events should not be reported on an SAE Form:Hospitalisations for:Protocol defined treatment.Pre-planned elective procedures unless the condition worsens.Treatment for progression of the patient’s cancer.Admissions or prolongations of hospitalisation due to social reasons.Progression or death because of the patient’s MF, as this information is captured elsewhere on the CRF.

The outcome of pregnancies of patients should be monitored and SAE data provided on congenital anomalies or birth defects.

Adverse events of special interest observed with fedratinib include:Encephalopathy, including Wernicke’s encephalopathy, or suspected cases of Wernicke’s encephalopathy with thiamine levels below normal range.

All cases of encephalopathy, of any grade, and whether or not the event is serious, should be reported using the SAE form.

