^c^To be performed at screening. An eye examination should be performed immediately/as soon as possible for any patients experiencing a decrease or loss of vision during treatment

^d^For women of childbearing potential, to be performed within 14 days of first dose of study drug, at the start of each cycle of treatment and at the end of treatment visit

^e^Haematology to include: haemoglobin, platelets, white blood count (WBC), neutrophils, lymphocytes, and blast count/percentage. May be ± 3 days prior to the start of each cycle

^f^Blast count/percentage as recorded by routine analyser differential, or manual differential from blood film

^g^Biochemistry to include: albumin, bilirubin, alanine transferase/aspartate aminotransferase, alkaline phosphatase, calcium, creatinine, potassium, glomerular filtration rate, total protein, urea, amylase or lipase, sodium, triglycerides, and cholesterol. May be ± 3 days prior to the start of each cycle

^h^Coagulation to include prothrombin time (PT) *or* PT ratio *or* international normalised ratio (INR) and activated partial thromboplastin time (APTT) *or* APPT ratio

^i^Virology to include hepatitis B, hepatitis C, and HIV

^j^Can have been performed at any point prior to registration

^k^Serious adverse events collected from the point of consent, adverse events from the start of trial treatment

The expected doses of each drug are shown in Table 3. An initial pre-treatment stage of fedratinib monotherapy is followed by combination therapy with ropeginterferon alfa-2b from cycle 1. Consecutive 28-day cycles comprise oral fedratinib taken once daily continuously, and subcutaneous injections of ropeginterferon alfa-2b administered on days 1 and 15 of each cycle.

**Table 3 Tab3:** Doses of fedratinib and ropeginterferon alfa-2b

Cycle number (each 28 days)	Fedratinib	Ropeginterferon alfa-2b
Pre-treatment	400 mg once daily	None
1	400 mg once daily	100 µg every two weeks
2	400 mg once daily	150 µg every two weeks
3	400 mg once daily	200 µg every two weeks
4	400 mg once daily	250 µg every two weeks
5–24	400 mg once daily	250 µg every two weeks

Patients will be treated for up to two years (24 cycles). On completion, patients are expected to revert to treatments routinely available as part of NHS care.

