### Trial outcomes

The primary outcome is tolerability of combination therapy. A patient is classified as not tolerating treatment if they discontinue either fedratinib or ropeginterferon alfa-2b due to drug-related toxicity, due to delays in treatment exceeding 28 consecutive days due to drug-related toxicity, or if a treatment toxicity-related death is reported, within four months of starting combination therapy.

The secondary outcomes are:Tolerability of combination therapy throughout the treatment course. A patient is classified as not tolerating treatment as per the definition for the primary outcome.Best overall response (complete plus partial response) assessed using International Working Group criteria (spleen size measure by palpation) [30] within 12 and 24 months from starting combination treatment. Patients who die or do not have a disease response recorded prior to the relevant time points will be classified as non-responders.The highest tolerated dose of ropeginterferon alfa-2b, in combination with fedratinib, achieved by each patient. To be tolerated, the dose must have been maintained for at least one complete cycle.Toxicity, defined to be any grade ≥ 3 AE, or a SAE of any grade. See the Adverse Events Reporting and Analysis section for details.Overall survival, defined as the time from starting combination therapy to date of death from any cause. Patients who are alive at the time of analysis or lost to follow-up will be censored at their date last seen.Progression-free survival, defined as the time from starting combination therapy to first event or death from any cause. An event is defined to be any of the following: an increase in bone marrow fibrosis, an increase in spleen size by > 5cm, or transformation to acute myeloid leukaemia. Patients who are alive and event-free at the time of analysis or lost to follow-up will be censored at their date last seen.Quality of life assessed using the myelofibrosis symptom assessment form (MFSAF) v4.0 [31] total symptom score at trial entry, and three-monthly during treatment.Bone marrow fibrosis, assessed using consensus definitions [32] at trial entry and six-monthly during treatment.

The *JAK2*^V617F^ clone size, measured at trial entry and three-monthly during treatment, is an exploratory outcome.

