#### Outcome analysis

For the primary outcome, the total number and proportion of patients tolerating four months of treatment will be reported alongside the associated 95% credible interval, using the total number of patients who started combination therapy as the denominator (including patients who failed to find any tolerable dose). Bayesian posterior probability plots will be presented alongside the probability that the true tolerability rate is greater than 70%.

Analyses of the secondary and exploratory outcomes will be descriptive in nature, with no hypothesis testing conducted.The total number and proportion of patients tolerating up to two years of combination therapy will be reported alongside the associated 95% credible interval, using the total number of patients who started combination therapy as the denominator.Best overall response rate will be presented as the number and proportion of patients achieving a response, overall and by response category, over the total number of patients receiving combination treatment.The number and proportion of patients will be reported against the highest tolerated ropeginterferon alfa-2b dose that each individual patient received, having followed dose escalation schedule.Toxicity will be presented as the number and proportion of patients experiencing one or more grade ≥ 3 AEs, or a SAE of any grade. This outcome will be analysed using the safety population.Overall and progression-free survival will be presented using Kaplan–Meier plots. The median time to event and survival estimates at one year will be presented with 95% confidence intervals where appropriate.The MFSAF v4.0 analyses will be presented as medians with interquartile ranges over time. Multi-level models may be used to compare changes in scores from baseline to 12 months if appropriate.Bone marrow fibrosis will be tabulated and presented graphically, with number and proportion of patients at each level reported. In addition to this, individual patient results will be plotted to show change over time at the patient level.The *JAK2*^V617F^ mutant allele frequency will be presented as medians and interquartile ranges over time, overall and split by highest dose of ropeginterferon alfa-2b tolerated and summarised using descriptive statistics. Individual patient plots will also be presented showing raw percentages.

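### The secondary toxicity outcome counts any grade 3 or higher AE, but laboratory values that change no treatment are not reported, so the proportion is biased low by an unknown, possibly small, amount

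*Protocol article*

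**What the plan says.** Trial outcomes lists toxicity among the secondary outcomes. It covers any AE of grade 3 or higher and any SAE, sets no causality condition, and adds "See the Adverse Events Reporting and Analysis section for details". Outcome analysis reports the "number and proportion of patients experiencing one or more grade" 3 or higher AEs, or an SAE of any grade, and states "This outcome will be analysed using the safety population". Grading follows "National Cancer Institute Common Terminology Criteria for Adverse Events (CTCAE), version 5.0".

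Adverse events reporting and analysis then limits what sites report: "Abnormal laboratory findings should only be reported if the event results in the early discontinuation of trial treatment, a dose modification, or interruption". It continues: "If a laboratory abnormality is one component of a diagnosis or syndrome, then only the diagnosis or syndrome should be recorded as an AE". Neither sentence exempts severe values.

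The laboratory data are nevertheless collected. Table 2 schedules haematology and biochemistry on day 1 of every cycle, on day 15 of pre-treatment and of cycles 1 and 2, and at the end-of-treatment visit. Its footnotes list the tests: "Haematology to include: haemoglobin, platelets, white blood count (WBC), neutrophils, lymphocytes, and blast count/percentage", and for biochemistry bilirubin, ALT/AST and amylase or lipase, among others. The analysis text in the article does not say that these values are graded or enter the toxicity outcome.

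**The concern.** The outcome is worded to include every severe AE, while the collection rule makes one class of severe finding depend on a treatment decision. A laboratory value of grade 3 or higher that leaves dosing unchanged can meet the words of the outcome and still be missing from the AE data from which the outcome is counted.

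The omission can only lower the proportion. It also brings attribution into an outcome defined without it, because a value thought to be due to the disease is less likely to lead to a dose change than one thought to be due to the drug. Safety is one of the three aspects, with tolerability and activity, on which the abstract says a phase III decision will draw. In a single-arm trial there is no concurrent group in which the same omission would cancel.

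**Working it through.** **The plan's own figure.** The article gives no figure for toxicity. Its one design figure concerns tolerability. With a Beta(1,1) prior and 23 of 30 patients tolerating treatment, the posterior is Beta(1+23, 1+7) = Beta(24, 8), and P(rate > 0.70) = 0.755, which agrees with the stated 76%. Nothing below depends on it.

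**Following one value through the rules.** Take a laboratory value of CTCAE grade 3 or higher.

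1. *Suspected to be caused by ropeginterferon.* The ropeginterferon section calls for a pause. A pause is an interruption, so the value becomes reportable and is counted.
2. *Suspected to be caused by fedratinib.* The dose rules are in Appendix 5, which is not shown. The fedratinib section names severe liver-test elevations and recurrent grade 4 haematological toxicity among the causes of a dose reduction after which re-escalation is not advised. Many such values should therefore change dosing and be counted.
3. *Part of a recorded diagnosis or syndrome, or of an SAE.* The diagnosis or the SAE can be counted.
4. *Worsening of a pre-existing condition.* The AE section allows reporting when the condition deteriorates by a CTCAE grade or more. It does not say which rule governs when that condition is itself a laboratory finding, for example anaemia present at entry that reaches grade 3 without a dose change.
5. *None of the above.* The value is not reported and cannot be counted.

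The fifth group consists chiefly of values judged unrelated to study drug. Cytopenias attributed to myelofibrosis are the obvious case: the Background names anaemia as a feature of the disease, and Table 1 sets entry limits for platelets and neutrophils but none for haemoglobin. Values in the fedratinib-only phase that trigger no dose rule also belong here.

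**Effect on the primary outcome.** Non-tolerance rests on discontinuation, a delay of more than 28 consecutive days, or a toxicity-related death. A laboratory finding that causes discontinuation or interruption meets the reporting rule. The primary outcome is not affected.

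**Size.** The documents give no rate of severe laboratory abnormalities, so this is an illustration on assumed inputs. Let c be the proportion counted as having toxicity under the plan. Let q be the share of the remaining patients whose only grade 3 or higher event is a laboratory value in the fifth group.

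Undercount = (1 − c) × q

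- c = 0.5, q = 0.1: 0.5 × 0.1 = 5 percentage points, or 1.5 of 30 patients.
- c = 0.5, q = 0.4: 0.5 × 0.4 = 20 points, or 6 of 30.
- c = 0.7, q = 0.1: 0.3 × 0.1 = 3 points, or 0.9 of 30.
- c = 0.3, q = 0.4: 0.7 × 0.4 = 28 points, or 8.4 of 30.
- q = 0: no undercount, whatever c is.

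Thirty is the recruitment target and is used only for scale; the safety population may differ in number. The direction follows from the text. The size depends wholly on q, which the documents do not give.

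**The case against.** The strongest reply is that the gap is narrow. Drug-suspected events of grade 3 or higher pause ropeginterferon, Appendix 5 may act in the same way for fedratinib, and the diagnosis, worsening-condition and SAE routes bring in others. This stands. A reader might infer that severe cytopenias and liver abnormalities are missed in general; the documents do not support that, because drug-suspected marrow and liver events are the ones most likely to change dosing and so be reported.

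Second, the definition refers openly to the AE section, so the two texts do not strictly contradict each other. That is fair. The proportion actually reported is still narrower than its label.

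Third, anaemia due to the disease arguably does not belong in a toxicity rate. That is a legitimate preference, but the outcome as defined sets no causality condition. Exclusion should then be stated rather than arise from a reporting rule.

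Fourth, laboratory tables usually belong in the SAP, which is not shown, and Appendices 5 and 8 are not shown either. Their absence from the article is not held against the plan. The point rests on an outcome and a collection rule that are both stated here. If the SAP already derives laboratory grades, only the labelling remains.

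**Conclusion.** The concern holds in a limited form. Values of grade 3 or higher that alter no treatment, and reach the AE data by no other route, are omitted from an outcome worded to include them. The proportion is biased downward and depends partly on attribution. This assumes that sites follow the reporting rule as printed and that laboratory grades are not added from another source.

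The size cannot be calculated. A reader might take an illustrative figure of 10 to 20 percentage points as an estimate, but any such figure rests on assumed inputs, and zero is possible. A reader might also infer that the trial's main safety conclusion or its decision rule is compromised. The documents do not support this: toxicity is one of several descriptive secondary outcomes without hypothesis testing, and the criterion for further investigation is a high probability that tolerability exceeds 70%, which is untouched.

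**What to change.** Keep the site reporting rule. From the scheduled haematology and biochemistry, derive CTCAE v5.0 grades and report:

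- the worst post-baseline grade for each parameter, beside its baseline grade;
- the proportion of patients with any grade 3 or higher laboratory value that worsened from baseline;
- that proportion combined with reported grade 3 or higher AEs and SAEs, each patient counted once.

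State which value is the baseline. The last one before the first fedratinib dose would match the start of the AE reporting period. Label the AE-only proportion as excluding laboratory abnormalities that did not change treatment.

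This needs some programming but no new visits, no extra site reporting and no change to treatment. The toxicity rate will look less favourable and may include disease-related cytopenias, which is why the baseline grades and the separate proportions should be shown. Scheduled samples will still miss short-lived abnormalities between visits, particularly from cycle 3, when only day 1 is sampled.

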### Collection and management of data and samples

FEDORA uses a secure online electronic remote data capture (eRDC) system to capture the CRF data. Access to the eRDC system is granted to individuals by the FEDORA Trial Office. Paper CRFs are also available as a backup. Data reported on each CRF should be consistent with the source data and any discrepancies explained. If information is not known, this must be clearly indicated on the CRF. All missing and ambiguous data will be queried. All sections are to be completed.

All trial records must be archived and securely retained for at least 20 years. No documents will be destroyed without prior approval from the sponsor, via the central FEDORA Trial Office. On-site monitoring will be carried out as required following a risk assessment and as documented in the Quality Management Plan. Any monitoring activities will be reported to the central Trial Office and any issues noted will be followed up to resolution. FEDORA is also centrally monitored, which may trigger additional on-site monitoring.

The CRCTU will hold the final trial dataset and will be responsible for the controlled sharing of anonymised clinical trial data with the wider research community to maximise potential patient benefit while protecting the privacy and confidentiality of trial participants. Data anonymised in compliance with the Information Commissioner’s Office requirements, using a procedure based on guidelines from the Medical Research Council Methodology Hubs, will be available for sharing with researchers outside of the trials team within 12 months of the primary publication.

Research samples collected during the trial will be stored at the Weatherall Institute for Molecular Medicine, and may be used for future ethically approved research if the patients who provided these samples have given their explicit consent.

### Trial organisation structure

The University of Birmingham will act as single sponsor: Research Governance & Integrity, Research Strategy and Services Division, [name]. Email: [contact]. The trial is being conducted under the auspices of the CRCTU, University of Birmingham according to their local procedures. The trial management group (TMG) is responsible for the day-to-day running and management of the trial. Members of the TMG include the Lead Investigator, Co-Investigators, Clinical Coordinators, the Trial Management Team Leader (or delegate), the Trial Biostatistician, the Trial Coordinator, and the Monitor. The TMG meet three-monthly during recruitment and will then do so at least yearly.

An independent TSC has been set up to oversee the conduct of FEDORA. The TSC is chaired by an independent Chair with other members including a second independent clinician, an independent statistician, and one patient advocate. The TSC operates in accordance with a trial specific charter based upon the template created by the Damocles Group and, therefore, performs the role of a data monitoring committee. The TSC met seven months after the commencement of recruitment and have met at least nine-monthly since. The TSC advises on whether the accumulated trial data, together with the results from other relevant research, justifies the continuing recruitment of further patients. Additionally, the committee supervises the conduct of the trial, monitoring progress including recruitment, data completeness, losses to follow-up, and deviations from the protocol.

### Confidentiality

Confidential information collected during the trial will be stored in accordance with the General Data Protection Regulation 2018. As specified in the patient information sheet and with the patients consent, patients will be identified using only their date of birth and unique trial ID number. Authorised staff may have access to the records for quality assurance and audit purposes. The Trials Office maintains the confidentiality of all patients’ data and will not disclose information by which patients may be identified to any third party other than those directly involved in the treatment of the patient, and organisations for which the patient has given explicit consent for data transfer (e.g., laboratory staff).

### Dissemination of results and publication policy

Results will be submitted for publication in a peer reviewed journal. The manuscript will be prepared by the TMG, and authorship determined by mutual agreement in line with ICMJE criteria. A lay summary of the results will be published on the ISRCTN Results and CRCTU Trials websites. The trial protocol will be made available on the ISRCTN website.

Any secondary publications and presentations prepared by investigators will be reviewed by the TMG.

### Trial status

Recruitment for the trial opened in Sep-2022 and is expected to last until 31-Mar-2025.

## Discussion

### Choice of trial design

FEDORA has been designed as a single arm, phase II trial to assess the tolerability, safety, and activity of ropeginterferon alfa-2b in combination with fedratinib. Both fedratinib and ropeginterferon have been shown to be well-tolerated as single agents, however, there is less information on the tolerability and activity of these treatments in combination. As such, a single arm design was chosen to determine the tolerability of the combination treatment whilst assessing for evidence of activity within the secondary outcomes of best overall response and progression-free survival. If this trial produces a high probability that the true tolerability of the combination treatment is at least 70%, then further investigation in a larger trial would be warranted. A Bayesian approach was taken as opposed to a standard frequentist approach to improve the interpretability of the results obtained.

The within-patient dose escalation regimen has been designed to ensure each patient reaches a personalised dose combination that they are able to tolerate. Furthermore, the risk to the patient is reduced by requiring tolerability to single-agent fedratinib to be established first, followed by an escalation of ropeginterferon alfa-2b from a level far below that expected to cause significant side effects.

Evidence from FEDORA will be used to determine whether a phase III trial of fedratinib and ropeginterferon-alpha is warranted.

